#### 7.4.5 Sex Hormones

Table 4-20 Temporal analysis of measured values of estradiol (pg/ml) (full analysis set, FAS)

| Visit    | Treatment group (N=XXX) | Placebo group (N=XXX) |
|----------|-------------------------|-----------------------|
| Baseline |                         |                       |

| Visit                    | Treatment group (N=XXX) | Placebo group (N=XXX) |
|--------------------------|-------------------------|-----------------------|
| N (NMissing)             | XXX                     | XXX                   |
| Median (IQR)             | XX.XX (XX.X, XX.X)      | XX.XX (XX.X, XX.X)    |
| 8 week                   |                         |                       |
| N (NMissing)             | XXX                     | XXX                   |
| Median (IQR)             | XX.XX (XX.X, XX.X)      | XX.XX (XX.X, XX.X)    |
| Change from baseline     |                         |                       |
| N (NMissing)             | XXX                     | XXX                   |
| Median (IQR)             | XX.XX (XX.X, XX.X)      | XX.XX (XX.X, XX.X)    |
| Between-group difference |                         |                       |
| Median (IQR)             | XX.XX (XX.X, XX.X)      |                       |
| P-value                  | XX.XX                   |                       |

Note: Between-group differences were compared using the Wilcoxon test.

Table 4-21 Temporal analysis of measured values of progesterone (nmol/L) (full analysis set, FAS)

| Visit                    | Treatment group (N=XXX) | Placebo group (N=XXX) |
|--------------------------|-------------------------|-----------------------|
| Baseline                 |                         |                       |
| N (NMissing)             | XXX                     | XXX                   |
| Median (IQR)             | XX.XX (XX.X, XX.X)      | XX.XX (XX.X, XX.X)    |
| 8 week                   |                         |                       |
| N (NMissing)             | XXX                     | XXX                   |
| Median (IQR)             | XX.XX (XX.X, XX.X)      | XX.XX (XX.X, XX.X)    |
| Change from baseline     |                         |                       |
| N (NMissing)             | XXX                     | XXX                   |
| Median (IQR)             | XX.XX (XX.X, XX.X)      | XX.XX (XX.X, XX.X)    |
| Between-group difference |                         |                       |
| Median (IQR)             | XX.XX (XX.X, XX.X)      |                       |
| P-value                  | XX.XX                   |                       |

Note: Between-group differences were compared using the Wilcoxon test.

Table 4-22 Temporal analysis of measured values of prolactin (ng/ml) (full analysis set, FAS)

| Visit                    | Treatment group (N=XXX) | Placebo group (N=XXX) |
|--------------------------|-------------------------|-----------------------|
| Baseline                 |                         |                       |
| N (NMissing)             | XXX                     | XXX                   |
| Median (IQR)             | XX.XX (XX.X, XX.X)      | XX.XX (XX.X, XX.X)    |
| 8 week                   |                         |                       |
| N (NMissing)             | XXX                     | XXX                   |
| Median (IQR)             | XX.XX (XX.X, XX.X)      | XX.XX (XX.X, XX.X)    |
| Change from baseline     |                         |                       |
| N (NMissing)             | XXX                     | XXX                   |
| Median (IQR)             | XX.XX (XX.X, XX.X)      | XX.XX (XX.X, XX.X)    |
| Between-group difference |                         |                       |
| Median (IQR)             | XX.XX (XX.X, XX.X)      |                       |
| P-value                  | XX.XX                   |                       |

Note: Between-group differences were compared using the Wilcoxon test.

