### 6.2 Sample Size Estimation

Based on the literature (Jiangsu Journal of Traditional Chinese Medicine, 2021, 53(8): 3 and Journal of Traditional Chinese Medicine, 2019(17): 5), the reduction in breast pain VAS score after two menstrual cycles of treatment with Danlu capsule is 3.2 points, while the reduction in the control group (placebo) is approximately 1.5 points, with a standard deviation of 3.4 points. The sample size for this superiority trial was calculated using a t-test. Based on a superiority margin of 0, a two-sided  $\alpha$  of 0.05, and  $\beta$  of 0.05 (power = 95%), with 1:1 allocation, the required sample size per group was determined to be 105 using PASS 21.0 software. Considering a dropout rate of 20%, the sample size is increased to 132 cases per group, resulting in a total of 264 cases.

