#### **Secondary Efficacy Endpoint Analysis:**

(1) Quality of life scale (SF-36) Score Changes at weeks 4, 8, and 12 (one month after discontinuation of treatment):

Group differences will be compared using MMRM, with the model including treatment group, visit, group-by-visit interaction, and baseline value as a covariate. Missing values will not be imputed. The analysis will be based on the actual data in the FAS.

(2) Anxiety and depression assessment scale score changes at weeks 4, 8, and 12 (one month after discontinuation of treatment):

Group differences will be compared using MMRM, with the model including treatment group, visit, group-by-visit interaction, and baseline value as a covariate. Missing values will not be imputed. The analysis will be based on the actual data in the FAS.

(3) Breast lump size changes at weeks 4 and 12 (one month after discontinuation of treatment):

Group differences will be compared using MMRM, with the model including treatment group, visit, group-by-visit interaction, and baseline value as a covariate. Missing values will not be imputed. The analysis will be based on the actual data in the FAS.

(4) Hormonal regulation indicators (serum estrogen, progesterone, prolactin) changes:

Group differences will be compared using the Wilcoxon test. The analysis will be based on the actual data in the FAS.

(5) Cytokine (IL-6, TNF- $\alpha$ ) changes:

Group differences will be compared using the Wilcoxon test. The analysis will be based on the actual data in the FAS.

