### 7.4 Efficacy Analysis

#### 7.4.1 Breast Pain Analysis

Table 4-1 Analysis of covariance (ANCOVA) of change in breast pain score at week 8 (full analysis set, FAS)

Table 4-2 Analysis of covariance (ANCOVA) of change in breast pain score at week 8 (per protocol set, PPS)

| Visit                       | Treatment group (N=XXX) | Placebo group (N=XXX) |
|-----------------------------|-------------------------|-----------------------|
| Baseline                    |                         |                       |
| N (NMissing)                | XXX                     | XXX                   |
| Mean $\pm$ SD               | XX.XX $\pm$ XX.XX       | XX.XX $\pm$ XX.XX     |
| 8 week                      |                         |                       |
| N (NMissing)                | XXX                     | XXX                   |
| Mean $\pm$ SD               | XX.XX $\pm$ XX.XX       | XX.XX $\pm$ XX.XX     |
| Change from baseline        |                         |                       |
| N (NMissing)                | XXX                     | XXX                   |
| Mean $\pm$ SD               | XX.XX $\pm$ XX.XX       | XX.XX $\pm$ XX.XX     |
| LS mean (SE)                | XX.XX (XX.XX)           | XX.XX (XX.XX)         |
| LS mean difference (95% CI) | XX.XX (XX.XX, XX.XX)    |                       |
| P-value                     | XX.XX                   |                       |

Note: Analysis of covariance (ANCOVA) was used, with treatment group and center as fixed effects, and baseline value as a covariate. Missing values were imputed using the last observation carried forward (LOCF) method.

Table 4-3 Temporal comparison of between-group differences in LSMEANS of change in breast pain score by

MMRM (full analysis set, FAS)

Table 4-4 Temporal comparison of between-group differences in LSMEANS of change in breast pain score by MMRM (per protocol set, PPS)

|                             | Treatment group (N=XXX) | Placebo group (N=XXX) |
|-----------------------------|-------------------------|-----------------------|
| Baseline                    |                         |                       |
| N (NMissing)                | XXX                     | XXX                   |
| Mean±SD                     | XX.XX±XX.XX             | XX.XX±XX.XX           |
| 4 week                      |                         |                       |
| N (NMissing)                | XXX                     | XXX                   |

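### The hormone and cytokine tables summarise the between-group difference as a median with IQR, which is undefined for two independent arms, and plan no confidence interval for the effect

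*Supplement*

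**What the plan says.** Section 5.1.2 of the SAP lists hormones and cytokines as secondary efficacy endpoints (4) and (5). For both, section 6.4.6 gives the method as "Group differences will be compared using the Wilcoxon test", on observed data in the full analysis set. It names no estimator of the difference and no interval.

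The shells are in section 7.4.5 (Tables 4-20 to 4-22: estradiol, progesterone, prolactin) and section 7.4.6 (Tables 4-23 and 4-24: TNF-α, IL-6). All five have the same layout. Each arm gets a median with IQR at baseline, at week 8 and for the change. A block headed "Between-group difference" follows, with a single entry for both arms: again a median with IQR, printed as one value and two limits, and then a P-value. The note adds only "Between-group differences were compared using the Wilcoxon test".

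The ANCOVA shell for breast pain (section 7.4.1) has an effect row that opens "LS mean difference (95% CI", and the MMRM shells whose bodies are shown have the same row.

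**The concern.** An IQR describes the spread of a set of observations. Section 3 describes a randomized, placebo-controlled trial with independent arms, so no participant has a between-group difference and no such set of observations exists. A programmer must choose what the cell means, and the choice falls outside the plan.

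The limits also stand where the other efficacy shells carry a 95% confidence interval, in a similar bracketed layout and next to a P-value. A reader will look to them for the precision of the effect and will not find it there. Section 1 names the mechanism of action among the points still to be clarified, and these five endpoints bear on it. As planned, each yields a test result without a usable statement of how well the effect is estimated.

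**Working it through.** **1. The plan's sample size.** This is needed only to fix n per arm. Section 6.2 gives the two expected VAS reductions: "treatment with Danlu capsule is 3.2 points, while the reduction in the control group (placebo) is approximately 1.5 points". It assumes an SD of 3.4, two-sided α of 0.05 and 95% power.
- Difference: 3.2 − 1.5 = 1.7.
- Normal approximation: 2 × (1.960 + 1.645)² × 3.4² / 1.7² ≈ 104 per arm.
- Noncentral t: power is 0.9483 at 104 and 0.9501 at 105, so 105 per arm, as stated.
- Dropout: 105 / (1 − 0.20) = 131.25, rounded up to 132 per arm and 264 in total, as stated.

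The plan's figures reproduce. I use n = 105 and n = 132 as the range. These numbers come from the VAS calculation, and the number of evaluable biomarker samples may differ.

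**2. Ways to fill the cell.**
- (a) A difference of the two medians, with some chosen spread. No natural pair of limits goes with it. Subtracting the quartiles arm by arm, for example, gives two numbers that under a pure shift both estimate the shift itself.
- (b) The median and quartiles of all treatment-minus-placebo pairs.
- (c) The quartiles of a resampling distribution of the estimated difference.

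**3. Reading (b), closed form.** Assume normal changes with SD 1 in each arm; the documents give no SD for any biomarker.
- IQR of a pairwise difference: 2 × 0.6745 × √2 = 1.91 SD, whatever the n.
- Width of the 95% Hodges-Lehmann interval: 2 × 1.96 × √((π/3) × (2/n)), which is 0.554 SD at n = 105 and 0.494 SD at n = 132.
- Ratio: 3.4 at n = 105 and 3.9 at n = 132.
- The pairwise IQR excludes zero only if the shift exceeds about 1.91 / 2 ≈ 0.95 SD. The standard error at n = 105 is 0.554 / 3.92 = 0.141 SD, so that is nearly seven standard errors.

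**4. Reading (b), simulation.** There were 1,000 trials per row. The interval is the 95% Hodges-Lehmann interval that inverts the Wilcoxon test (large-sample limits). Normal changes had SD 1 and a shift of 0.5. Skewed changes were differences of two standard lognormal values, with a shift of 0.7. All of these are assumptions.

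| Changes | n per arm | IQR width / CI width | 95% CI excludes 0 | Pairwise IQR excludes 0 |
|---|---|---|---|---|
| Normal | 105 | 3.42 | 95.2% | 0.2% |
| Normal | 132 | 3.84 | 98.4% | 0.1% |
| Skewed | 105 | 3.80 | 84.7% | 0.0% |
| Skewed | 132 | 4.29 | 93.4% | 0.0% |

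Where the test detects the shift in 85% to 98% of trials, the printed quartiles still span zero in at least 99.8% of them.

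**5. Reading (c).** Quartiles of a sampling distribution bound a 50% interval. Under approximate normality its half-width is 0.6745 standard errors against 1.96 for a 95% interval: 1.96 / 0.6745 = 2.9 times too narrow.

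Readings (b) and (c) err in opposite directions, and nothing in the plan selects one.

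**The case against.** The strongest reply is that the row is a descriptive summary, openly labelled as an IQR, and that nothing in the plan presents it as a confidence interval. That is correct. A reader might infer that the tables print mislabelled error bars; the documents do not support this. The fault is an undefined summary in the effect row and no interval planned for the effect.

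A reader might also infer that the biomarker effects could not be read at all. That goes too far. Each shell gives the median change with IQR for both arms and the Wilcoxon P-value, so the direction and rough size of the difference remain visible. What is missing is its precision.

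Nor does it follow that the limits must be too wide, or by one fixed factor. That holds only under the pairwise reading and the assumed distributions; the resampling reading reverses the direction. Under the pairwise reading, moreover, the median of the differences is itself the Hodges-Lehmann estimate, so the point estimate would already match the test and only the limits would be unsuitable.

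Finally, these are secondary mechanistic endpoints, and no planned test depends on the row. This bears on severity. It does not define the statistic or supply an interval, and no other section of the SAP does so.

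**Conclusion.** The point holds as a minor reporting error. In all five biomarker shells the effect row asks for a statistic with no defined meaning for independent arms, and no confidence interval is planned for these endpoints.

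The size depends on how the cell is filled. With pairwise quartiles the limits are about 3.4 to 4.3 times as wide as a 95% Hodges-Lehmann interval and do not narrow with n. With resampling quartiles they are about 2.9 times too narrow. The pairwise range rests on 105 to 132 evaluable participants per arm and on assumed normal or skewed changes; the 2.9 rests on an approximately normal estimator. That neither reading gives the precision of the effect does not depend on those assumptions.

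The Wilcoxon P-values, the within-arm summaries, the primary VAS analysis, the sample size and the type I error are untouched. The contrast with the other efficacy tables is limited to the ANCOVA shell and the MMRM shells whose bodies are shown; the body of Table 4-14 is not in the text available.

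**What to change.** In Tables 4-20 to 4-24, replace the median with IQR in the between-group block by *Hodges-Lehmann estimate of the between-group shift in change from baseline (95% CI)*. This estimate and its interval correspond to the planned Wilcoxon test. State it in section 6.4.6 items (4) and (5) and in the five table notes. Keep median with IQR in the within-arm rows.

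The cost is one row in five shells, one added sentence in each of the two items and the notes, and a trivial computation. No test, endpoint or sample size changes. There is one small downside: the estimate can be read as a treatment shift only if the arms differ mainly in location, which skewed hormone or cytokine changes may not satisfy. The table note should say so.

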#### 7.4.6 Cytokines

Table 4-23 Temporal analysis of measured values of tumor necrosis factor- $\alpha$  (pm/ml) (full analysis set, FAS)

| Visit        | Treatment group (N=XXX) | Placebo group (N=XXX) |
|--------------|-------------------------|-----------------------|
| Baseline     |                         |                       |
| N (NMissing) | XXX                     | XXX                   |
| Median (IQR) | XX.XX (XX.X, XX.X)      | XX.XX (XX.X, XX.X)    |
| 8 week       |                         |                       |
| N (NMissing) | XXX                     | XXX                   |
| Median (IQR) | XX.XX (XX.X, XX.X)      | XX.XX (XX.X, XX.X)    |

| Visit                    | Treatment group (N=XXX) | Placebo group (N=XXX) |
|--------------------------|-------------------------|-----------------------|
| Change from baseline     |                         |                       |
| N (NMissing)             | XXX                     | XXX                   |
| Median (IQR)             | XX.XX (XX.X, XX.X)      | XX.XX (XX.X, XX.X)    |
| Between-group difference |                         |                       |
| Median (IQR)             | XX.XX (XX.X, XX.X)      |                       |
| P-value                  | XX.XX                   |                       |

Note: Between-group differences were compared using the Wilcoxon test.

Table 4-24 Temporal analysis of measured values of interleukin-6 (pm/ml) (full analysis set, FAS)

| Visit                    | Treatment group (N=XXX) | Placebo group (N=XXX) |
|--------------------------|-------------------------|-----------------------|
| Baseline                 |                         |                       |
| N (NMissing)             | XXX                     | XXX                   |
| Median (IQR)             | XX.XX (XX.X, XX.X)      | XX.XX (XX.X, XX.X)    |
| 8 week                   |                         |                       |
| N (NMissing)             | XXX                     | XXX                   |
| Median (IQR)             | XX.XX (XX.X, XX.X)      | XX.XX (XX.X, XX.X)    |
| Change from baseline     |                         |                       |
| N (NMissing)             | XXX                     | XXX                   |
| Median (IQR)             | XX.XX (XX.X, XX.X)      | XX.XX (XX.X, XX.X)    |
| Between-group difference |                         |                       |
| Median (IQR)             | XX.XX (XX.X, XX.X)      |                       |
| P-value                  | XX.XX                   |                       |

Note: Between-group differences were compared using the Wilcoxon test.

## 7.5 Safety Analysis

### 7.5.1 Adverse Event Analysis

Table 5-1 Analysis of incidence of adverse events (Safety set, SS)

| Indicator                                            | Treatment group (N=XXX) | Placebo group (N=XXX) | P-value |
|------------------------------------------------------|-------------------------|-----------------------|---------|
| N                                                    | XXX                     | XXX                   |         |
| Adverse events n (%)                          | XX (XX.X)               | XX (XX.X)             | X.XXX   |
| Adverse reactions n (%)                       | XX (XX.X)               | XX (XX.X)             | X.XXX   |
| Serious adverse events n (%)                  | XX (XX.X)               | XX (XX.X)             | X.XXX   |
| Serious adverse reactions n (%)               | XX (XX.X)               | XX (XX.X)             | X.XXX   |
| Adverse events leading to withdrawal n (%)    | XX (XX.X)               | XX (XX.X)             | X.XXX   |
| Adverse reactions leading to withdrawal n (%) | XX (XX.X)               | XX (XX.X)             | X.XXX   |
| Adverse events leading to death n (%)         | XX (XX.X)               | XX (XX.X)             | X.XXX   |

Note: Adverse events with a relationship to the study drug classified as “definitely related”, “probably related”, or “possibly related” are considered drug-related TEAEs (i.e., ADRs).

Table 5-2 Systemic analysis of adverse events (safety set, SS)

Table 5-3 Systemic analysis of adverse reactions (safety set, SS)

Table 5-4 Systemic analysis of serious adverse events (safety set, SS)

Table 5-5 Systemic analysis of serious adverse reactions (safety set, SS)

Table 5-6 Systemic analysis of adverse events leading to withdrawal from the study (safety set, SS)

Table 5-7 Systemic analysis of adverse reactions leading to withdrawal from the study (safety set, SS)

| SOC           | Treatment group (N=XXX) |                 | Placebo group (N=XXX) |                 |                       |
|---------------|-------------------------|-----------------|-----------------------|-----------------|-----------------------|
|               | PT                      | Number of cases | Number of occurrences | Number of cases | Number of occurrences |
| N             |                         | XXX             |                       | XXX             |                       |
| Summary n (%) |                         | XXX (XX.X)      | XXX                   | XXX (XX.X)      | XXX                   |
| SOC1 n (%)    |                         | XXX (XX.X)      | XXX                   | XXX (XX.X)      | XXX                   |
| PT1 n (%)     |                         | XXX (XX.X)      | XXX                   | XXX (XX.X)      | XXX                   |
| PT2 n (%)     |                         | XXX (XX.X)      | XXX                   | XXX (XX.X)      | XXX                   |
| ...           |                         |                 |                       |                 |                       |
| SOC2          |                         | XXX (XX.X)      | XXX                   | XXX (XX.X)      | XXX                   |
| PT1 n (%)     |                         | XXX (XX.X)      | XXX                   | XXX (XX.X)      | XXX                   |
| PT2 n (%)     |                         | XXX (XX.X)      | XXX                   | XXX (XX.X)      | XXX                   |
| ...           |                         |                 |                       |                 |                       |
| SOC3          |                         | XXX (XX.X)      | XXX                   | XXX (XX.X)      | XXX                   |
| PT1 n (%)     |                         | XXX (XX.X)      | XXX                   | XXX (XX.X)      | XXX                   |
| PT2 n (%)     |                         | XXX (XX.X)      | XXX                   | XXX (XX.X)      | XXX                   |
| ...           |                         |                 |                       |                 |                       |
